## Abstract

**Background:**

Monitoring motor symptoms in patients with Parkinson disease (PD) presents significant challenges due to the complex nature of symptom progression, variations in medication responses, and the fluctuations that can occur throughout the day. Traditional neurological visits provide only a limited perspective of a patient’s overall condition, with challenges in achieving accurate and objective assessments of symptoms. To bridge this gap, extended monitoring in nonclinical settings could play a critical role in personalizing treatments and improving their efficacy. Wearable devices have emerged as potential tools for assessing PD symptom severity; however, studies integrating both in-clinic and free-living conditions, as well as multiday monitoring, remain scarce. Defining digital biomarkers that provide valuable insights into motor symptoms could enable comprehensive monitoring and tracking of PD in various contexts, facilitating more precise medication adjustments and the implementation of advanced therapeutic strategies.

**Objective:**

This study aims to collect a dataset to support the proposal and definition of digital biomarkers of PD motor symptoms using wearable devices. Data will be collected both in a supervised setting and continuously in a remote, free-living context during participants’ normal daily activities; the study will include patients with PD and healthy controls. The goal is to identify reliable digital biomarkers that can effectively distinguish patients with PD from healthy controls and classify disease severity in both supervised and unsupervised free-living environments.

**Methods:**

This paper outlines a protocol for an observational case-control study aimed at assessing motor symptoms in patients with PD using a smartwatch. The smartwatch will record accelerometer, gyroscope, and physical activity data. Participants will be instructed to perform a series of exercises guided via a smartphone. Measurements will be collected in 2 settings: a supervised clinical environment, with motor symptoms assessments conducted at the beginning and end of the study, and in an unsupervised free-living context for 1 week. In both settings, participants will be required to wear the smartwatch while performing the same set of exercises. In their daily routine, participants will be required to wear the smartwatch continuously throughout the day, removing it only at night for charging.

**Results:**

Participant recruitment and data collection started in December 2024 and will continue until spring 2025. The study aims to enroll 20 participants with PD and 20 healthy controls.

**Conclusions:**

It is anticipated that the generation of a dataset of accelerometer and gyroscope signal data recorded from patients with PD at various stages of the disease, alongside data from a control group, will enable robust comparative and impactful analyses. In addition, the study seeks to develop analytical techniques capable of tracking PD symptoms in real-life scenarios, both in everyday settings and clinical environments.

**Trial Registration:**

ClinicalTrials.gov NCT06817772; https://clinicaltrials.gov/study/NCT06817772

**International Registered Report Identifier (IRRID):**

DERR1-10.2196/72820

## Introduction

### Background

In the context of an increasingly aging society characterized by an inverted population pyramid, the treatment and management of neurodegenerative diseases represent an important challenge. In 2013, the World Health Organization recognized neurodegenerative diseases as “a global health problem that must be addressed without delay for humanitarian, social, and economic reasons” [1]*.*

Parkinson disease (PD) exemplifies this issue, with the number of individuals affected rising by 250% between 1990 and 2015 [2]. In Spain, a new case of PD is diagnosed approximately every 45 minutes, with 15% of these cases occurring in individuals aged < 45 years [3]. PD is a progressive neurodegenerative disorder characterized by the selective degeneration of dopaminergic neurons in the substantia nigra pars compacta, which supports the corticosubcortical network, which facilitates limbic, associative, cognitive, and motor functions [4]. In early stages, PD often exhibits nonmotor dysfunctions, including impairments in working memory, executive function, attention, visuospatial capacity, and semantic fluency, which may eventually progress to dementia [5].

In advanced stages, motor symptoms (such as tremor, bradykinesia, postural instability, and rigidity) and nonmotor symptoms (including cognitive decline, mood disorders, sleep disturbances, and autonomic dysfunction) become more pronounced, significantly affecting patients’ quality of life [6,7].

Currently, there is no cure for PD. Treatment strategies typically involve pharmacological and surgical interventions, often complemented by nonpharmacological therapies [8]. Pharmacological treatments focus on restoring dopamine levels to preserve motor function for as long as possible [9]. While effective in managing hypokinesia (loss of movement) and tremor, these therapies remain beneficial within a therapeutic window of 5 to 10 years, after which 50% to 80% of patients develop dyskinesias (involuntary muscle movements). In addition, certain patients exhibit resistance to these treatments [10].

Nonpharmacological interventions are crucial for enhancing patients’ quality of life [11]. These include traditional treatments such as physical exercise, physiotherapy, occupational therapy, or cognitive training, among others [12-14]. Experimental approaches, including noninvasive neurostimulation techniques such as transcranial direct current stimulation [15], are also being explored for their potential to improve symptom management.

The diagnosis of PD is primarily clinical, relying on a detailed anamnesis based on information from the patient and their family, combined with a physical examination [16]. These consultations are used to conduct clinical assessments, adjust medications, and prescribe exercises or therapies. Several clinical scales support this process, with the Movement Disorder Society-Unified Parkinson’s Disease Rating Scale (MDS-UPDRS) [17] being the most widely used. However, the time allocated per patient during these visits is limited [18]. Reflecting this constraint, numerous resources, including guidelines, websites, and individualized workshops, have been developed to help patients and caregivers prepare effectively for their neurologist appointments [19-22].

Recent studies have highlighted the suboptimal accuracy of clinical diagnoses for PD, as the techniques are inadequate for capturing the nuanced and fluctuating nature of PD symptoms, which can vary significantly throughout the day [23]. Clinical assessments, conducted infrequently during brief consultations, fail to provide a comprehensive understanding of patients’ conditions in their everyday lives [24]. This limitation underscores the need for continuous monitoring tools to complement periodic clinical evaluations.

To enhance diagnostic resources for objective monitoring, digital health technologies, particularly wearable devices, offer significant potential for optimizing health management [25]. These technologies can serve as complementary clinical tools, supporting tasks such as early diagnosis and the objective monitoring of PD symptoms over time [26]. Wearable devices provide a discreet and user-friendly solution that not only reduces the burden on patients to remember and manually record information about their symptoms but also offers systematically organized data on symptom evolution [27]. This can be achieved by using digital biomarkers [28], which enable the objective assessment of disease progression and the impact of treatments or therapeutic interventions in chronic conditions such as PD.

### BioClite Project

BioClite (Digital Biomarkers for the Assessment of Motor Status in Parkinson’s Disease Patients With Clinical and Therapeutic Application) is a project funded by the Ministry of Science and Innovation of Spain (No. PID2021-123708OB-I00) that aims to enhance PD monitoring using wearable technology.

The BioClite project responds to the growing need for objective assessment tools to improve the management and long-term monitoring of PD using wearable devices, specifically smartwatches. By using this technology, the project aims to improve the accessibility of medical care and eliminate physical barriers between patients and health care providers.

Prior studies have used wearable devices to assess motor symptoms. In the study by Samà et al [29], bradykinesia severity was evaluated using a waist-worn device; in the study by Di Lazzaro et al [30], several wearable devices were used to assess several MDS-UPDRS tasks; Coates et al [31] focused on gait parameters using an inertial measurement unit placed on the lower back; and in the study by Antonini et al [32], multiple motor symptoms were assessed using a commercially available wearable device. According to a review on wearable devices for PD monitoring [28], the most commonly used wearables incorporate inertial measurement units, such as accelerometers and gyroscopes, typically embedded in smartwatches, wristbands, or worn on the lower back or ankles.

However, previous technology-based approaches have presented several limitations. Many required bulky or intrusive equipment, limiting their practicality for long-term or home-based use. Others were constrained to controlled environments, reducing ecological validity and overlooking symptom fluctuations in daily life. Furthermore, user compliance was often hindered by complex device management or lack of feedback. Importantly, some earlier systems did not sufficiently address data privacy concerns, raising potential risks regarding the handling of sensitive personal information, particularly when combined with the use of artificial intelligence models [33].

This study advances this field by implementing a dual-monitoring approach: guided exercises conducted in controlled environments, where participants perform specific tasks to capture motor patterns associated with PD, and free-living activities, where data are collected from participants in uncontrolled environments during their daily routines outside of clinical or laboratory settings without direct supervision and under natural conditions.

One of the daily-life activities is egg beating, an activity often identified by patients with PD as one that made them aware of their condition; this activity is performed under both supervised and unsupervised conditions. This approach not only allows for direct comparison between clinical and real-world data but also introduces an ecological, patient-centered perspective that is largely absent from previous research, which has typically relied on standardized clinical tasks. By including free-living monitoring, this methodology allows for continuous data collection without interrupting patients’ everyday activities, providing a more natural and unobtrusive experience compared to traditional methods.

Data labeling plays a crucial role in the project and is carried out using 2 main methods: algorithmic tagging, where custom-designed algorithms automatically analyze collected signals to identify significant motor events, and the use of external beacons and markers to link time points with contextual information, improving the accuracy of the tagging process. The combination of these approaches can support the collection of a comprehensive, annotated dataset that supports the development of algorithms for PD detection, status prediction, and personalized therapeutic strategies.

Through the collection of motor activity data, primarily in real-world environments, the project aims to develop digital biomarkers that provide valuable insights into PD symptoms, particularly tremors and bradykinesia. The protocol detailed in this paper describes a study designed to leverage digital biomarkers for PD detection, with the objective of distinguishing patients with PD from healthy individuals and enabling early-stage disease assessment. This approach allows continuous monitoring of symptoms and evaluation of therapeutic effects, thereby supporting personalized treatment strategies and improving the management of the disease.

The BioClite project contributes to more precise symptom tracking and the advancement of wearable technology in PD management by enabling continuous and unobtrusive monitoring, ultimately enhancing patient care and advancing scientific research in the field.

## Methods

### Inclusion and Exclusion Criteria

For the PD cohort, the main inclusion criterion is a diagnosis of PD based on the United Kingdom Brain Bank criteria. All participants in this group were recruited from Asociación Parkinson Madrid (APM), ensuring access to a well-defined population actively engaged in PD care and support.

To ensure a representative sample, efforts will be made to achieve a gender balance across the study population. In addition, participants must meet an age requirement ranging from 45 to 80 years, reflecting the study’s focus on middle-aged and older populations typically affected by PD [34].

The control participants are not selected based on strict age alignment with the PD patients, as both groups are recruited and analyzed concurrently. Instead, efforts will be made to ensure that the 2 groups exhibit comparable means and SDs with respect to age, such as pairing the recruitment of healthy controls with that of participants with PD or dividing participants into smaller age groups (eg, 55-60, 61-65 years) and ensuring a similar number of healthy controls and participants with PD within each group.

While this design choice may introduce variability, age will be included as a covariate in statistical analyses to account for its potential impact on the results. In addition, prioritizing inclusivity over strict matching allows a broader understanding of how the proposed biomarkers may generalize across diverse populations.

The common inclusion criteria established for participants with PD and control groups are as follows:

Wear the study devices on the hand most affected by the condition and dominant (for patients with PD) or the dominant hand (for controls). In both cases, this should be the hand primarily used in the free-living activities.Be capable of performing prescribed exercises independently.Maintain daily functioning without dependence on caregivers.

Specific inclusion and exclusion criteria for the PD group have been designed to enhance better representative of the sample, given that the study focuses on the detection and initial stages of the disease, as participants with advanced PD often exhibit evident motor symptoms that are more readily identifiable; however, they may also experience impairments that could limit the feasibility or effectiveness of wearable monitoring technologies [35]:

Eligible participants must have minimal or mild disease severity, defined by a Hoehn and Yahr scale score of ≤2.5.Participants must not experience motor symptom fluctuations throughout the day.Individuals who have undergone deep brain stimulation, used dopamine infusion pumps, or have conditions mimicking PD symptoms (eg, progressive supranuclear palsy, Lewy body dementia, multiple system atrophy, or other parkinsonian syndromes) are excluded.

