### Data Analysis

The resulting database from the data collection campaign will comprise signals from the 3 axes of the smartwatch’s accelerometer and gyroscope. These data will be divided into 3 distinct parts. First, it will include the evaluation of the sequence of 8 Monipar exercises, conducted both in supervised and labeled conditions following the MDS-UPDRS III scale, as well as in unsupervised free-living conditions. Second, it will encompass the performance of the specific free-living exercise, 1 minute of beating eggs, performed under supervised conditions at the association and under unsupervised free-living conditions. Finally, the database will contain the daily recording of 4 hours of free-living activity, accompanied by the physical activities performed during the day and participant-completed notebooks detailing activities such as eating, resting, and taking medication.

A comprehensive data analysis will be proposed to identify appropriate indicators and validate their effectiveness. Various scenarios will be proposed based on the collected data, providing insights into the potential applicability of these biomarkers in diverse clinical and therapeutic contexts.

A set of biomarkers will be defined for the identification of patients with PD by comparing their data with those of healthy participants. Another collection of biomarkers will be calculated to predict MDS-UPDRS scores in patients with PD using the labeled sessions, enabling a more detailed understanding of the relationship between the recorded signals and clinical evaluations.

In addition, a comparative analysis will be undertaken using the previous or new biomarkers between measurements collected in supervised clinical contexts and those recorded in unsupervised, free-living conditions. Similarly, the validity and performance of the proposed biomarkers will be examined across different age groups, given the motor variability present among various age ranges. This will help determine the consistency and reliability of the data across different contexts. Furthermore, the study will explore the correlation between the specific free-living exercise, which is strongly linked to bradykinesia, and the MDS-UPDRS exercises of the Monipar sequence. This correlation will be examined for both data collected at the APM and at the participants’ homes, providing insights into how specific activities reflect the motor symptoms in patients with PD across diverse settings.

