Depending on the amount of extracted features, it may be beneficial to reduce their number, as a manageable and well-defined set of characteristics is essential for establishing reliable biomarkers.

Statistical and probabilistic analyses will be performed using the proposed features to identify potential biomarkers that correlate with the various PD symptoms being studied. These biomarkers may be consistent across all symptoms or distinct for each symptom, as well as for different activities.

Furthermore, artificial intelligence classification models will be developed using the proposed features. Given the medical context of this study case, it is crucial that the models are interpretable and explainable. To achieve this, machine learning algorithms such as random forests or decision trees will be used, as these models can be subjected to explainable artificial intelligence techniques. In addition, deep learning models will be incorporated to enhance the predictions made by the machine learning models. The most relevant features will be extracted from the models to identify digital biomarkers for motor symptoms of PD.

The evaluation of the classification models will be assessed through a confusion matrix, alongside metrics such as sensitivity, specificity, or accuracy. Other performance measures, such as the area under the receiver operating characteristic curve, could be considered to offer a more thorough evaluation of the model’s effectiveness.

In unsupervised measurements conducted at participants’ homes, the MDS-UPDRS score determined in the clinical setting can be used as a benchmark to evaluate its alignment with the results obtained from these unsupervised measurements. However, considering the intrinsic subjective nature of MDS-UPDRS labeling, unsupervised learning methods, such as association rules or clustering algorithms, will also be explored to analyze the assessment of the exercises performed to uncover data-driven patterns. This approach aims to provide a complementary perspective and reduce reliance on subjective evaluations.

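### Age balance between PD patients and controls is left to non-binding efforts, and the stated covariate adjustment does not reach the classifier accuracy measures

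*Protocol article*

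**What the plan says.** Methods, Inclusion and Exclusion Criteria, sets an age range of 45 to 80 years and then states: "The control participants are not selected based on strict age alignment with the PD patients, as both groups are recruited and analyzed concurrently". The next sentence offers a softer aim, that "efforts will be made to ensure that the 2 groups exhibit comparable means and SDs with respect to age". Two ways of doing so are given as examples: pairing the recruitment of controls with that of patients, or forming small age groups and "ensuring a similar number of healthy controls and participants with PD within each group". Neither is required, and no acceptable difference is stated. The article concedes that the choice may add variability and answers that "age will be included as a covariate in statistical analyses to account for its potential impact on the results". It also defends the choice on the ground that "prioritizing inclusivity over strict matching allows a broader understanding of how the proposed biomarkers may generalize across diverse populations".

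The Objective in the Abstract is to "identify reliable digital biomarkers that can effectively distinguish patients with PD from healthy controls". Methods, Data Analysis, pursues this partly by statistical analysis of features and partly by random forests, decision trees and deep learning. For the models it says: "The evaluation of the classification models will be assessed through a confusion matrix, alongside metrics such as sensitivity, specificity, or accuracy". AUC is mentioned as a further option. No handling of age is stated for these measures. The same section plans to examine biomarker performance by age group, "given the motor variability present among various age ranges".

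**The concern.** A PD-versus-control comparison should differ by disease and, as far as possible, by nothing else that moves the signal. Age moves it, as the article itself accepts. The reason given for not matching strictly, that both groups are recruited and analysed at the same time, controls for calendar time and has no bearing on whether the groups are of similar age.

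The article therefore leans on covariate adjustment for whatever imbalance remains. In a regression of a feature on group and age, that is sound. A confusion matrix, a sensitivity or an AUC from a classifier has no group coefficient to adjust. If the groups differ in age and the features vary with age, the classifier gains from the age difference and the gain is counted as discrimination of PD. Resampling by participant would not expose this, because the same gap sits in every fold. Features taken from the models as biomarkers could then partly be markers of age. The database is to be published, so later users would inherit any imbalance.

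**Working it through.** The article states no age mean, SD, expected age difference or target accuracy, so there is no figure of its own to reproduce. What follows is an illustration under stated assumptions.

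**Inputs from the article:** 20 PD and 20 control participants; ages 45 to 80. **Assumed:** normal ages with the same SD in both groups, SD = 6, 8 or 10 years; a range of mean age gaps *g*.

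**1. Discrimination from age alone, no PD signal.** AUC = Φ(g / (SD·√2)). For example, with g = 5 and SD = 8: 5 / 11.31 = 0.442, and Φ(0.442) = 0.671.

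| Age gap | SD 6 | SD 8 | SD 10 |
|---|---|---|---|
| 3 years | 0.638 | 0.605 | 0.584 |
| 5 years | 0.722 | 0.671 | 0.638 |

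**2. A sensor feature with no PD effect but correlation *r* with age.** AUC = Φ(r·g / (SD·√2)). With SD 8 and r = 0.3, 0.5, 0.7 (assumed), this gives 0.532, 0.553, 0.574 at 3 years and 0.553, 0.587, 0.621 at 5 years. The leak through the features is smaller than the age-only figure but not zero.

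**3. How large a gap chance alone would leave without any balancing.** Standard error of the mean difference = SD·√(2/20), which is 1.90, 2.53 and 3.16 years for SD 6, 8 and 10. The probability of a gap above 3 years is 0.11, 0.24 and 0.34; above 5 years it is 0.01, 0.05 and 0.11. These assume source populations with equal age distributions and no balancing effort. They describe what the efforts have to prevent, not what the plan is expected to produce.

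**4. What band balancing would achieve.** Simulated PD ages (mean 65, SD 8, limited to 45 to 80), with each control drawn at random from the same 5-year band as a PD participant: the mean difference stays within about 0.92 years in 95% of samples. Age-only AUC at that limit is Φ(0.92 / 11.31) = Φ(0.081), about 0.53.

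**5. Ways of handling age in a classifier.** Simulated linear classifier trained on 20 + 20, five features each correlated 0.5 with age, no PD effect, SD 8; mean AUC in new participants:

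| Age gap | Age ignored | Age added as predictor | Features standardised on age in controls |
|---|---|---|---|
| 0 | 0.50 | 0.50 | 0.50 |
| 3 years | 0.53 | 0.54 | 0.51 |
| 5 years | 0.575 | 0.60 | 0.53 |

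With a gap, ignoring age leaves the bias in, entering age as a predictor enlarges it, and standardising features on age removes most of it. Some remains, since the age slope is estimated from only 20 controls. Balance at recruitment is therefore the first line of defence and analysis the second.

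**The case against.** The strongest reply is that the article plans more than a covariate. A reader might infer that controls are deliberately left unaligned on age. The text does not support that: it rejects only strict alignment, and the next sentence aims at comparable means and SDs through paired recruitment or age-band balancing, within a common age range. If those efforts succeed, the bias is close to zero, as step 4 shows. This stands, and it limits the point to a residual gap.

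A reader might also infer that the safeguard itself will inflate the result because age will be fed to the classifiers. Nothing says so. The models are to use the proposed features, which are described as extracted from the signals. The middle column of step 5 shows why this should be ruled out explicitly; it is not a description of the plan.

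Nor is it right that adjustment for age cannot work for accuracy measures. Age-standardised features and covariate-adjusted ROC methods exist, and a broad reading of statistical analyses does not exclude them. The article simply names none. Classifiers are also not the only route to biomarkers, and for the feature-level analyses the covariate does its job.

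The planned look at age groups is a further safeguard, but a weak one. Ages 45 to 80 make seven 5-year bands, so 20 / 7 is about three participants per group per band, and the Study Design section itself says the sample limits detailed subgroup analyses.

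Finally, this is an exploratory study. The standard error of an accuracy near 50% in 40 people is √(0.25 / 40), about 8 percentage points, so a modest bias would be hard to see. That limits the practical weight, but bias does not average out as sampling error does.

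Detail on model fitting can properly sit in an analysis plan that is not shown. The point here is narrower: the article states a rationale that does not bear on age balance and a safeguard that, as worded, does not reach the measures it names.

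**Conclusion.** The point holds in a limited form. Age balance rests on efforts with no required method and no tolerance. The reason given for not matching strictly is not a reason. The stated covariate adjustment protects feature-level regressions but, as worded, not the sensitivity, specificity, accuracy or AUC of the PD-versus-control classifiers. Any residual age gap can therefore be counted as discrimination of PD.

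The consequence ranges from almost nothing, if band balancing is carried out, to the age-only AUC values in step 1 if a gap of 3 to 5 years remains. Those values rest on assumed normal ages with equal SDs of 6 to 10 years. Leakage through the sensor features depends further on their correlation with age, which is unknown. None of these figures forecasts the bias in this study. They show that nothing the article states would protect the classifier results should a gap occur. The correction is a cheap improvement worth making, not a reason to doubt the design as a whole.

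**What to change.** 1. **Inclusion and Exclusion Criteria.** Make the age-band option already listed the rule: fill the remaining control places so that each 5-year band holds the same number of controls as PD participants. Delete the rationale that refers to concurrent recruitment and analysis.
2. **Data Analysis.** Confine age as a covariate to the feature-level regressions. State that age is not offered as a predictor in the PD-versus-control classifiers. Report an age-only classifier on the same held-out participants as a benchmark. Beside the unadjusted measures, report an age-adjusted AUC, with features standardised on age using the control regression fitted within each training fold.

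**Cost.** Part 1 restricts which control volunteers can be invited, so control recruitment may be slightly slower. Part 2 uses data already collected and remains available if recruitment has closed. The reported accuracy may look less favourable.
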